##### Secondary Outcome Measures

A visual analog scale (VAS) will be used to measure patients' alcohol cravings on a scale ranging from *0* to *10*, with *0* indicating no craving at all and *10* indicating extreme craving. The scale will be presented visually on a ruler, and patients will be asked to indicate their mean and peak level of craving during the past 30 days (57, 58).

The Alcohol Abstinence Self-Efficacy Scale is a 40-item measure of patients' temptation to drink and their perceived self-efficacy in abstaining from drinking in 20 different situations that represent typical cues for drinking. Twenty items pertain to temptation, and 20 items pertain to self-efficacy. Patients will rate each item on a scale ranging from *not at all* (0) to *extremely* (4). The measure comprises the following sub-scales: (1) negative affect; (2) social interaction and positive states; (3) physical and other concerns; and (4) withdrawal and urges to drink. Both the temptation and perceived efficacy total score can range from 0 to 80 (60).

The Readiness-to-Change Questionnaire Treatment Version (RTCQ-TV) is a 12-item measure of patients' stated intentions to change their drinking, which includes the following sub-scales: (1) pre-contemplation, (2) contemplation, and (3) action stages. Four items pertain to each sub-scale, and each item is rated on a 5-point Likert Scale ranging from strongly agree (−2) to strongly disagree (+2). The total score can range from −24 to +24 (61, 75).

The Positive and Negative Affect Schedule (PANAS) is a 20-item measure of the patient's affective states, which includes two sub-scales: (1) positive affect and (2) negative affect. Ten items pertain to each sub-scale, and each item is rated on a 5-point scale ranging from *1* (*not at all*) to *5* (*very much*). The total score can range from 20 to 100 (62).

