### Statistical Analysis

The intent-to-treat principle will be followed in the analyses to evaluate the intervention. A repeated-measures MANOVA with groups as the between-participants factor and assessment time-point as the within-participants factor will be used to test the efficacy of the intervention across the assessment points. Efficacy would be indicated by a significant Time X Study Group interaction. Each of the significant interactions will be followed up with *post-hoc* tests to identify the source of the interaction. Potential demographic covariates (e.g., age, education, income) will also be considered by using MANCOVA. Further, attrition rate at each follow-up time point will be evaluated. Baseline characteristics of participants who remain in the study will be compared with those who have been lost to follow-up. A multiple imputation (MI) approach that adjusts for uncertainty arising from missing data (76, 77) will also be conducted to evaluate the main findings.

Based on MacKinnon (78) mediational procedures, a series of regression analyses will be conducted to test the hypothesized mediational relationships among the outcome variables, i.e., that reductions in *alcohol AB* and *cravings* will partially mediate improvements in the outcome measures. Several ancillary interaction effects will also be evaluated, although they are not hypothesized to be significant. They include potential interactions between the intervention received and patients' drinking history, affective states, and cognitive flexibility. Although the intervention is intended to be effective for all AUD patients, it is important to test this assumption by evaluating whether the intervention is effective for specific sub-groups of patients.

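### The only scores defined for the RTCQ-TV and the PANAS are totals across opposed sub-scales, with no reverse scoring or direction of benefit stated

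*Protocol article*

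**What the plan says.** All the scoring rules stand in the protocol article under Secondary Outcome Measures.

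- **RTCQ-TV.** "The Readiness-to-Change Questionnaire Treatment Version (RTCQ-TV) is a 12-item measure of patients' stated intentions to change their drinking". Its sub-scales are "1) pre-contemplation, (2) contemplation, and (3) action stages", and "Four items pertain to each sub-scale". Every item has the same anchors, "ranging from strongly agree (−2) to strongly disagree (+2). The total score can range from −24 to +24".
- **PANAS.** A 20-item scale "which includes two sub-scales: (1) positive affect and (2) negative affect", with ten items each, rated 1 to 5. "The total score can range from 20 to 100".
- **Self-efficacy scale.** Here the two constructs are kept apart: "Both the temptation and perceived efficacy total score can range from 0 to 80".

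For the RTCQ-TV and the PANAS, the total is the only score whose range is given. No sub-scale is said to be reversed, and no direction is named as better.

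The Measures section also names affect among the secondary outcomes. Its list omits readiness to change, which appears only under the Secondary Outcome Measures heading. The Statistical Analysis section judges efficacy by a significant group-by-time interaction and plans to test whether the intervention interacts with "drinking history, affective states, and cognitive flexibility". It does not say whether totals or sub-scales enter these analyses.

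**The concern.** A total is useful when its parts point the same way. Here they do not. Positive and negative affect move in opposite directions when mood improves. Endorsing pre-contemplation items means not being ready to change, while endorsing action items means the reverse. Adding them with one sign lets gains on one part offset gains on the other.

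Two uses are at stake. As outcomes, the totals could show little or nothing when both parts improve, and a significant interaction would not show which arm did better. As a moderator, a PANAS total cannot separate a patient with high positive and low negative affect from one with the opposite pattern.

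The self-efficacy scale makes the gap visible. In the same section, temptation and efficacy, which are also opposed, keep separate totals.

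**Working it through.** **Inputs** (all from Secondary Outcome Measures): RTCQ-TV, 3 sub-scales of 4 items, each item −2 (strongly agree) to +2 (strongly disagree). PANAS, 2 sub-scales of 10 items, each item 1 to 5.

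**1. The stated ranges reproduce as sums over all items.**

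- RTCQ-TV: 12 × (−2) = −24; 12 × (+2) = +24. One sub-scale: 4 × (±2) = ±8.
- PANAS: 20 × 1 = 20; 20 × 5 = 100. One sub-scale: 10 × 1 = 10 to 10 × 5 = 50.

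**2. The ranges do not show whether a sub-scale is reversed.** Reversing pre-contemplation (P becomes −P) leaves −24 to +24. Reversing negative affect (NA becomes 60 − NA) leaves 20 to 100. The ranges fit either scoring, and the text states no reversal.

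**3. PANAS.** Raw total = PA + NA; reversed total = PA + (60 − NA).

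| Profile | PA | NA | Raw total | NA reversed |
|---|---|---|---|---|
| Best mood | 50 | 10 | 60 | 100 |
| Worst mood | 10 | 50 | 60 | 20 |
| Before | 25 | 30 | 55 | 55 |
| After a clear improvement | 35 | 20 | 55 | 75 |

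More generally, let PA rise by 1 unit and NA fall by k units. The raw total changes by 1 − k and the reversed total by 1 + k.

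| k | Raw change | Reversed change |
|---|---|---|
| 0 | 1 | 1 |
| 0.5 | 0.5 | 1.5 |
| 1 | 0 | 2 |
| 1.5 | −0.5 | 2.5 |

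Cancellation is complete only at k = 1. For k between 0 and 1 it is partial, and above 1 the raw total falls although both parts improve. Conversely, PA up 5 alone and NA up 5 alone both raise the raw total by 5, one being an improvement and the other a worsening.

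**4. RTCQ-TV.** Raw total = P + C + A; with pre-contemplation reversed, −P + C + A. Agreement is negative, as stated.

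| Profile | P | C | A | Raw total | P reversed |
|---|---|---|---|---|---|
| Pre-contemplation | −8 | +8 | +8 | +8 | +24 |
| Action, contemplation items rejected | +8 | +8 | −8 | +8 | −8 |
| Action, contemplation items endorsed | +8 | −8 | −8 | −8 | −24 |
| Moderate shift, before | −2 | 0 | +2 | 0 | +4 |
| Moderate shift, after | +2 | 0 | −2 | 0 | −4 |

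In every row, P and A sum to 0, so the raw total equals C. Between fully opposed profiles, only the contemplation items move the score. Under the stated anchors, reversing pre-contemplation gives the total a direction, but a higher value then means less ready.

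**The case against.** The strongest reply is that the section describes instruments and does not define endpoints. It names the sub-scales and their item counts, cites scoring sources for both scales, and says only what a total can range over. Nothing in the article says the totals will be analysed. The choice of score level may stand in the full protocol or a statistical analysis plan, neither of which is shown. The ranges also fit reverse scoring. All of this stands, so the consequence has to be stated conditionally.

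A reader might go further and infer four things that the text does not support:

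- **That a real improvement will cancel out.** This needs the raw total to be used and the shifts to be equal and opposite. With unequal shifts the loss is partial.
- **That every stage of change gives the same RTCQ-TV total.** The value +8 for each stage arises only if a patient strongly agrees with four items and strongly disagrees with the other eight. An action-stage patient who endorses the contemplation items scores −8.
- **That coding agreement as negative is itself an error.** Changing the sign of a whole score alters no test and no absolute effect size. What is missing is a statement of direction.
- **That a main result is at risk.** These are secondary measures, the Measures section does not list readiness to change among them, and the moderator analyses are ancillary and not expected to be significant.

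The reply does not remove the point. The article goes beyond leaving scoring open: it gives one score range per scale, a total across opposed parts, while handling the neighbouring scale differently. A reader who followed the text would sum the items.

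**Conclusion.** The point holds as a poorly fixed score on two secondary measures. If the totals are used as written, without reversal, the PANAS total is 60 at both the best and the worst profile, and the RTCQ-TV total reduces to the contemplation items when pre-contemplation and action are fully opposed. A group-by-time effect on either total, or moderation by a PANAS total, then has no reading as benefit or harm.

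This rests on two assumptions that the article neither confirms nor excludes: that the totals are what is analysed, and that no sub-scale is reversed. The cancellation is full for equal and opposite shifts and partial otherwise.

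Weekly mean drinking, the primary outcome, and the sample size do not depend on it. It is still worth settling before outcome data are seen, so that the choice between totals and sub-scales cannot follow the results.

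**What to change.** Replace both totals with sub-scale scores, as outcomes and, for affect, as moderators:

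- **PANAS:** positive affect, 10 to 50, higher is better; negative affect, 10 to 50, lower is better.
- **RTCQ-TV:** pre-contemplation, contemplation and action, each −8 to +8, with the meaning of a high score stated for each.
- **If one RTCQ-TV score is wanted:** reverse pre-contemplation and state which direction means more ready.
- **Moderation:** state that the affect interactions use the two PANAS sub-scales.

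This is a change of wording and scoring. The same items are collected, so no new data are needed. The cost is a few more secondary scores to report.

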### Statistical Analysis

The intent-to-treat principle will be followed in the analyses to evaluate the intervention. A repeated-measures MANOVA with groups as the between-participants factor and assessment time-point as the within-participants factor will be used to test the efficacy of the intervention across the assessment points. Efficacy would be indicated by a significant Time X Study Group interaction. Each of the significant interactions will be followed up with *post-hoc* tests to identify the source of the interaction. Potential demographic covariates (e.g., age, education, income) will also be considered by using MANCOVA. Further, attrition rate at each follow-up time point will be evaluated. Baseline characteristics of participants who remain in the study will be compared with those who have been lost to follow-up. A multiple imputation (MI) approach that adjusts for uncertainty arising from missing data (76, 77) will also be conducted to evaluate the main findings.

Based on MacKinnon (78) mediational procedures, a series of regression analyses will be conducted to test the hypothesized mediational relationships among the outcome variables, i.e., that reductions in *alcohol AB* and *cravings* will partially mediate improvements in the outcome measures. Several ancillary interaction effects will also be evaluated, although they are not hypothesized to be significant. They include potential interactions between the intervention received and patients' drinking history, affective states, and cognitive flexibility. Although the intervention is intended to be effective for all AUD patients, it is important to test this assumption by evaluating whether the intervention is effective for specific sub-groups of patients.

A power analysis (79, 80) was conducted using G^*^Power for a repeated-measures MANOVA with α = 0.05; effect size (ES) of *f* =0.20; power = 0.90; groups *k* = 3; and time-points measurements = 4. It showed that 88 participants will be required for the final analyses in each of the four cells (total *N* = 264). Prior evaluations identified *f* s of 0.30 (AB) and 0.37 (weekly mean drinking) and an *f* of 0.42 (situational confidence to resist drinking) on outcome measures for sub-clinical excessive drinkers (36). Further, in a study that used the intervention as an add-on treatment for clinical participants with a substance-use disorders other than AUD, effect sizes of *f* s = 0.33 (drug-specific AB), 0.34 (number of relapses), 0.32 (temptation to use) and 0.37 (self-confidence to resist temptation) were identified (42). Also, an unpublished study conducted with detoxified drug-abusers found *f* s of 0.39 (drug-specific AB), 0.18 (number of relapses), and 0.35 (temptation to use) (81). A second power analysis for a MANOVA with special effects and interactions was conducted to test the dosage-effect across groups (α = 0.05; EF *f*
^2^(*v*) = 0.06; power = 0.90; *k* = 3; predictors = 3; and response variables = 8), which yielded an *N* of 220. Attrition in similar studies has usually ranged from 10 to 15% (41, 42). Assuming a somewhat higher attrition rate (20%), which is not unlikely (82, 83), indicates that 317 (264 + [264·0.20]) participants should be tested at baseline for an analysis using listwise deletion of missing cases, although a multiple imputation (MI) analysis will also be conducted to verify that results converge across missing data assumptions. The projected sample size is sufficient for the planned data analyses, including mediational analyses based on Fitz and MacKinnon's guidelines (84).

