## Background

Alcohol-use disorder (AUD), as defined by DSM-5 criteria, is very common in the Western world, with a 12-month prevalence of 14% and a lifetime prevalence of 29% (1). Furthermore, AUD is the most prevalent and most harmful of all substance-use disorders (2, 3) and is among the leading causes of illness, disability, and mortality (4, 5). The high prevalence and severity of AUD underscore the importance of having easily available and effective treatments.

Overall, evidence-based psychological treatments, such as cognitive-behavioral therapy (CBT), have shown to be effective in the short term (6). During CBT, patients with an AUD are taught methods to help them identify high-risk situations for relapse. They also learn coping strategies for avoiding alcohol in high-risk situations. Patients are, however, supposed to learn these strategies by applying explicit and controlled cognitive techniques rather than practicing the strategies while being exposed to alcohol *in vivo* (7–9). Recovering patients often experience a relapse when they are exposed to alcohol and related stimuli in real-life, and they can only later analyze the consequences of their behavior. Patients with an AUD initially respond well to evidence-based psychological treatments, but as many as 50% of them relapse within 6 months after treatment discharge (10–12). This indicates that CBT and other evidence-based psychological treatments do not address all the crucial cognitive dysfunctions associated with maintaining an addiction; thus, they may not prepare patients to deal with their inevitable confrontation with alcohol cues in real life in Western societies.

One shortcoming of current psychological treatments is that they mainly target explicit and controlled cognitive dysfunctions. However, according to dual process models of addictive behaviors, confrontation with alcohol cues *in vivo* is influenced by two semi-independent cognitive systems: (1) a fast associative *impulsive* system, which is involved in the automatic evaluation of alcohol-related stimuli in the environment in terms of their emotional and motivational significance and which initiates approach or avoidance responses; and (2) a slow and controlled *reflective* system, which is involved in the regulation of the automatic and implicit responses elicited by the impulsive system, and which is responsible for explicit and controlled, higher-order cognitive processes (13–16).

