### Primary Treatment at the Outpatient Alcohol Clinics

At treatment entry, patients will be offered detoxification, if needed, before their primary treatment at one of the outpatient clinics is initiated. The primary treatment lasts 3 months and consists of both a pharmacological and a psychological treatment. The pharmacological treatment includes treatment with disulfiram and acamprosate. Naltrexone or nalmefene is also offered when deemed appropriate. The psychological treatment consists of cognitive-behavioral therapy (CBT), which is provided during hour-long individual or group sessions and typically includes eight sessions. The therapist and patient jointly plan the course of the patient's treatment. The treatment typically includes psychoeducation, functional analysis of drinking situations, and the development of coping strategies. The strategies include waiting out until an urge passes rather than acting on it, thinking about the negative consequences of drinking, thinking about the positive consequences of sobriety, consuming healthy alternative foods and beverages, problem-solving, and homework assignments between sessions. Therapists conduct the psychological treatment; they include nurses and social workers who have been specifically trained to deliver the range of therapies. Supervision takes place frequently, and psychiatrists regularly monitor patients' progress during the treatment (47).

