#### Clinical Outcomes

##### Primary Outcome Measures

Alcohol consumption will be measured with the Alcohol Timeline Follow-back (TLFB) method. It involves using a calendar to help the patient retrospectively recall the number of drinks that he/she consumed on each day during the previous 3 months (59, 72). The results will be used to calculate various alcohol consumption measures, including weekly mean drinking, which will be the primary outcome measure.

To validate the TLFB, hair samples from the patients will be tested for ethyl glucuronide (ETG) by liquid chromatography-tandem mass spectrometry (LC-MS/MS). This biological marker of alcohol consumption will be collected and analyzed according to the Society for Hair Testing (73, 74).

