## Discussion

The present study will investigate whether (1) the AACTP as an add-on intervention increases the effectiveness of a primary evidence-based treatment, and (2) a gamified version of AACTP can be successfully delivered *via* a smartphone application as an add-on. As mentioned in the introduction, the alcohol ACTP has been evaluated in community samples of excessive drinkers, for whom reductions in AB and alcohol consumption were observed post-treatment and at follow-up (32, 36, 37). In the first experimental study, it was found that individuals with harmful alcohol use (drinking > 50 units per week for men and > 35 units per week for women) showed reductions in both AB and alcohol consumption at post-treatment, and these reductions were maintained at a 3-month follow-up (32). In this initial study, the participants served as their own controls, which is a commonly used method in an initial evaluation of a new intervention (85). Hence, after recruitment and assessment, there was, in accordance with this alternative tradition, a waiting period before ACTP was started, and during this period there was no change in either AB or alcohol consumption, but there was a decline in both measures following the introduction of the AACTP intervention 1 month later (32). Similarly, a second randomized controlled study of a sub-clinical sample of hazardous drinkers (22–50 units per week for men and 15–35 units per week for women) and persons with harmful alcohol use found that the ACTP (compared to a non-active control group) was effective in decreasing alcohol consumption at post-treatment and at the 3-month follow-up, but the reductions had attenuated at the 6-month follow-up (36). A third randomized controlled study investigated whether the AATCP could be successfully delivered *via* a fully automated web-based delivery pathway to a community sample of hazardous drinkers. At post-intervention, a reduction in both alcohol craving and alcohol consumption was found in the AACTP group compared to an active sham-control group. However, the effects on alcohol consumption were not maintained at the 3-month follow-up (37). Finally, a fourth study tested a gamified AACTP delivered though a smartphone application in another community sample of hazardous drinkers (18–40 years old). Results indicated that reductions of up to 40% in alcohol consumption had occurred several months after the training (86).

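### Testing weekly mean drinking by a four-time-point Time x Group MANOVA, with baseline as an outcome level, may leave low power for a realistic percentage reduction; baseline drinking belongs in the model as a covariate

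*Protocol article*

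**What the plan says.** Under Primary Outcome Measures, the Timeline Follow-back calendar yields several consumption measures, "including weekly mean drinking, which will be the primary outcome measure". Each assessment looks back 3 months.

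Under Statistical Analysis, the test is stated as: "A repeated-measures MANOVA with groups as the between-participants factor and assessment time-point as the within-participants factor will be used to test the efficacy". The criterion is: "Efficacy would be indicated by a significant Time X Study Group interaction". The covariates mentioned there, for a MANCOVA, are demographic (age, education and income as examples). Baseline drinking is not among them.

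The power calculation in the same section uses "power = 0.90; groups *k* = 3; and time-points measurements = 4", with f = 0.20 and alpha 0.05. The Abstract lists four assessments (baseline, post-treatment, 3 and 6 months), so baseline is one of the four levels of the time factor.

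Two statements bear on the likely shape of the outcome. The Background says of patients after evidence-based treatment that "as many as 50% of them relapse within 6 months after treatment discharge". The section on primary treatment says: "The pharmacological treatment includes treatment with disulfiram and acamprosate", alongside cognitive-behavioural therapy and detoxification where needed. The article gives no mean, SD, range or share of abstainers for weekly drinking in this population.

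**The concern.** Drinking quantity in treated patients is probably right-skewed, with some exact zeros after treatment, and it follows a pre-treatment window of high and variable intake. The chosen test handles such data inefficiently in two ways.

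- **Degrees of freedom.** An effect that is much the same at all follow-ups is a single contrast per arm comparison. The interaction spreads the test over every time contrast.
- **Baseline noise.** With baseline as an outcome level, the effect is measured as change from baseline. The full spread of baseline drinking then enters the error, instead of being used to explain follow-up drinking.

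At stake is a false negative. The planning effect is in SD units and is not translated into drinks per week, so a worthwhile percentage reduction could correspond to an f well below 0.20.

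**Working it through.** **1. The plan's own figure.** For the interaction with k = 3 and m = 4: df1 = (k-1)(m-1) = 6, s = 2, df2 = 2(N-4), noncentrality = s x f² x N.

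- N = 264: noncentrality = 2 x 0.04 x 264 = 21.12, df2 = 520, power 0.950.
- N = 221: noncentrality = 17.68, df2 = 434, power 0.900.

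The stated power of 0.90 therefore needs 221. The planned 264 (88 x 3) gives 0.95, so the mismatch is on the safe side.

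**2. Does the shape of the data break the test at f = 0.20?** No. Assumptions: baseline mean 35 drinks/week, 50% zeros at follow-up, drinkers' mean 15 or 35, log-SD 0.8 or 1.2, correlation 0.5. With the effect scaled to f = 0.20, raw-scale MANOVA power was 0.949-0.956 and type I error 0.031-0.044. Normal data with the same means and covariances gave the same power to within about 5 points in every scenario run. What matters is the size of the effect relative to the variances, not non-normality as such.

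**3. What does f = 0.20 mean in drinks?** In those four settings it needs a shift of 19.0-23.5 drinks/week against a follow-up mean of 7.5-17.5, more than the whole mean. This is not general. With log-SD 0.5 and no zeros, 40% less drinking gave f = 0.288 and power 1.00.

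**4. Why baseline as an outcome costs power.** Let B and F be the SDs of baseline and follow-up, with correlation r.

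- Variance of change: F² + B² - 2rBF.
- Residual variance with baseline as a linear covariate: F²(1 - r²).
- Difference: (B - rF)², which is never negative.

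One-window illustration with assumed values. Half the patients drink, median 15, log-SD 0.8. Drinkers' mean = 15 x exp(0.32) = 20.66 and mean square = 225 x exp(1.28) = 809.2. Including zeros, the mean is 10.33 and F² = 404.6 - 106.7 = 297.9, so F = 17.3. Baseline median 40 gives B = 40.6 at log-SD 0.7 and B = 12.8 at log-SD 0.3. Take r = 0.5:

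| Baseline log-SD | Change variance | Adjusted variance | Ratio |
|---|---|---|---|
| 0.7 | about 1,248 | 223 | 5.6 |
| 0.3 | about 241 | 223 | 1.08 |

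The penalty is thus large or small according to baseline spread, which the article does not give.

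**5. Simulated power.** 88 per arm, follow-up median 15 among drinkers, log-SD 0.8 or 1.1, baseline median 40, log-SD 0.3 or 0.7, correlation 0.6. The last column is arm A against arm B in one window with baseline adjustment.

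| Effect in arm A | Raw MANOVA | Baseline-adjusted raw mean, one window |
|---|---|---|
| 50% zeros, 40% less among drinkers | 0.08-0.31 | 0.31-0.52 |
| Abstinence 50% to 65% | 0.07-0.19 | 0.19-0.28 |
| Abstinence 65% and 30% less | 0.10-0.52 | 0.53-0.76 |
| 30% zeros, 40% less | 0.13-0.70 | 0.46-0.80 |
| 10% zeros, 40% less | 0.17-0.97 | 0.69-0.97 |

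Null rejection was 0.031-0.060.

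A separate run compared the MANOVA with the baseline-adjusted mean of all three follow-ups under a sustained effect. Power was 0.08-0.96 and 0.25-1.00 respectively. The adjusted analysis was higher in every setting with a difference in means, and its null rejection was at or below about 0.05.

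**6. Would a log transform alone do?** Not reliably. Under the assumptions of step 2 widened to log-SD 0.5-1.2 and correlation 0.5-0.8, an abstinence effect (65% against 50%) gave 0.06-0.22 raw and 0.37-0.52 on log(1 + drinks). For 40% less among drinkers only, with 50% zeros, it was 0.09-0.45 raw and 0.11-0.18 log.

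**The case against.** The strongest reply is that the plan's test is valid and adequately powered for the effect it was sized on. That stands. The article also cites f = 0.37 for weekly mean drinking itself, well above 0.20. That figure comes from sub-clinical excessive drinkers, so its transfer to treated patients is uncertain, but it is evidence against assuming a small effect.

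Three stronger readings are tempting and are not supported.

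- **That the outcome will be analysed untransformed.** The article names no transformation, but it does not rule one out either. An article may leave this to the analysis plan, so silence is no defect.
- **That half the follow-up values will be zero.** The 50% is an upper figure for relapse from background literature. Relapse is not the complement of zero drinks in a 3-month window: a single drink makes the weekly mean non-zero. Treatment goals are recorded per patient, so abstinence is not stated as everyone's aim.
- **That most of the power is lost.** This depends wholly on the assumed distributions and effect. The simulated range runs from 0.08 to 0.96.

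Nor is the cited figure of "reductions of up to 40% in alcohol consumption" a benchmark for this trial. It comes from community hazardous drinkers, and the article describes no control comparison for it.

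What remains does not rest on silence: the article itself fixes the interaction test, the four time-points and hence baseline as an outcome level.

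**Conclusion.** The concern holds in a limited form. For a quantity that is probably skewed with some zeros after treatment, the planned test spends 6 degrees of freedom and adds baseline noise to the comparison. Power for a realistic percentage reduction may therefore be low. This is a matter of efficiency, not validity.

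Under the stated assumptions, power was 0.08-0.96 for the raw MANOVA and 0.25-1.00 for the baseline-adjusted follow-up mean. The gain is large when baseline drinking varies widely and small when it does not. None of the distributional inputs comes from the article, and the comparison assumes an effect sustained over the three windows. The direction of the gain is well supported; its size in this trial is unknown.

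**What to change.** Keep weekly mean drinking as the primary outcome. Analyse the three post-baseline windows in a longitudinal model with log baseline drinking as covariate, and test the arm effect on mean drinking averaged over follow-up with robust or bootstrap standard errors. Beside f = 0.20, state the reduction in drinks per week it represents under named assumptions.

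Report a two-part analysis (any drinking; amount when drinking) as supporting, not as the primary test. Its joint test rejected in 55-100% of simulated trials in which mean weekly drinking was about equal across arms, so it does not test the declared outcome. Its amount part also compares groups selected after randomisation.

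The cost is a change of analysis wording, best made before outcome data are seen by arm. It needs no new data and no more patients. The downside is that one average effect is less sensitive to a benefit confined to a single window, so the window-specific estimates should be reported as well.
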